#### Tenofovir testing

To assess PrEP adherence, tenofovir-diphosphate levels will be assessed at months 3, 6, 12, 18, and 24. Dried blood spots (DBS) will be prepared from venous blood and spotted on Whatman protein saver cards. Drug concentration testing will occur at the University of Cape Town Division of Pharmacology laboratory using DBS TDF testing protocols [60].

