### Sample size and power calculations

A sample size was calculated to have 80% power to detect differences in the proportion of participants adhering to PrEP among the three study arms (Aim 2) using the chi-square test for independence with two degrees of freedom, with an alpha of 0.05, and assuming an attrition rate of 10% for those who (1) withdraw voluntarily from the study, (2) initiate on PrEP but withdraw due to adverse events (e.g. hepatic or renal abnormalities), or (3) become ineligible for PrEP (e.g. seroconvert). The effect size estimate was informed by prior experience from the field, where an effect size of 0.30 has been found between ART clients receiving some adherence support and those receiving none. However, we use a more conservative effect size of 0.15, to account for the fact that adherence support may not lead to the same gains in adherence among HIV-negative PrEP clients as it does with HIV-positive ART clients. The sample size was calculated to be 160 per arm (480 total).

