### Primary and secondary outcomes

For Aim 1, our primary outcome will be the proportion of eligible individuals accepting PrEP as part of CBCT services. Secondary outcomes will include (1) stratification of PrEP initiation by both location and CBCT platform; (2) in-depth qualitative understanding of PrEP initiation; (3) correlates of immediate, delayed, and no PrEP initiation; and (4) comparison of sexual behaviours, risk profiles, and self-perception of risk in immediate, delayed, and never acceptors. Using the IMB model to inform the selection of variables and contextualization of results, an assessment of determinants of PrEP uptake will include (1) socio-demographic factors, (2) risk behaviours, (3) self-perception of risk, (4) previous knowledge of PrEP and perception of those taking PrEP, (5) partner characteristics and HIV status, (6) HIV-related stigma, and (7) screening scores for depression, substance abuse, and social support. Baseline STIs will be used as an independent marker of sexual risk behaviour, and to validate self-reported sexual risk behaviours and self-perception of risk.

For Aim 2, the primary outcome will be a comparison of TFV-DP levels by study arm at months 3, 6, 12, 18, and 24, with a 12-month primary outcome and 24-month assessment of intervention durability. Based on cumulative adherence behaviour, as measured in iPrEX OLE [14], adherence will be categorized as (1) *low adherence* (≤ 3 tablets per week; ≤ 699 fmol/DBS punch), and (2) *high adherence* (4–7 tablets per week; ≥ 700 fmol/DBS punch). Analysis of primary outcomes will be conducted on an intention-to-treat basis. Secondary outcomes will include (1) predictors of PrEP adherence after adjusting for study arm, socio-demographic factors, exposure to adherence support activities, and risk profiles; (2) characterization of changes in sexual behaviours and risk profiles following PrEP initiation; (3) proportion of individuals who discontinue PrEP and factors associated with discontinuation; (4) proportion of individuals who discontinue but subsequently restart PrEP and characteristics associated with this subgroup; (5) factors associated with of patterns of PrEP use; and (6) profiles of individuals that may benefit more from group-based vs. individualized adherence support.

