### Data analysis

Descriptive statistics (e.g. means, standard deviations/variances, medians with inter-quartile ranges, and frequency distributions) will be used to describe participant demographic characteristics. The chi-squared statistic test will be used for categorical variables whereas T-test (parametric) or Wilcoxon rank sum test (non-parametric) will be applied for continuous variables. Transformations of outcome variables will be explored and performed if appropriate. Multivariate logistic regression models will be performed to examine associations between covariates. Since data is collected on one subject over time, the data will be treated as longitudinal data. Generalized linear mixed effect models will be fitted to determine associations of interest with time and intervention effects included as fixed effects and allowing for subject-specific random effects. Alternatively, generalized estimating equations can be used to account for any correlations of repeated data measures, when assessing determinants of PrEP adherence at time points provided we have balanced data with ignorable missing patterns. Time-to-event analysis will be conducted using Kaplan-Meier plots. To determine possible associations with covariates, a Cox-proportional hazard will be used. If the proportional hazard assumption does not hold, an accelerated failure time model will be used. Missing data due to loss to follow-up is inadvertent and inevitable. The extent of missing data will be assessed in the primary analysis. The primary analysis will be conducted under the assumption of data Missing at Random (MAR). As such, longitudinal likelihood-based data analysis, utilizing all the observed pre-deviation data from each participant will be employed. Thereafter, multiple imputation (MI) method will be employed under the primary MAR assumption, and Rubin’s rule will be followed to combine results. Sensitivity to deviation from the MAR assumption will be investigated. Intention to treat (ITT) assessment with complete case approaches where necessary will be implemented in cases of non-adherence to randomization assignment. Depending on the extent of non-adherence, the “as treated (AT)” approaches may be employed to analyse participants according to the intervention received regardless to their randomized allocation. A marker of level of adherence can also be included in the models. Patterns of PrEP use will be identified using latent class models or clustering techniques and the association of factors with these latent classes will be examined using multinomial logistic regression modelling. For all statistical investigations, tests for significance will be two-tailed. Analyses will be conducted using STATA 13.0 or R version 4.

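### Regressing PrEP-use class on factors allows classification error to be ignored, so associations can be biased and intervals can under-cover if classes separate poorly (minor, one secondary outcome)

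*Protocol article*

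**What the plan says.** The Data analysis section of the protocol article covers this in one sentence. First, "Patterns of PrEP use will be identified using latent class models or clustering techniques". Then, "the association of factors with these latent classes will be examined using multinomial logistic regression modelling". It does not say which variables define a pattern, how many classes are expected, how a participant is placed in a class, or how uncertainty about her class enters the regression.

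The analysis serves an Aim 2 secondary outcome. Primary and secondary outcomes lists "factors associated with of patterns of PrEP use" as its fifth item, and Table 1 carries a similar entry.

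The repeated biological measure that could define patterns is drug level: Tenofovir testing says that "tenofovir-diphosphate levels will be assessed at months 3, 6, 12, 18, and 24". That is at most five values per participant.

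**The concern.** A latent class is not observed. It is inferred from a few noisy indicators, and some participants are placed in the wrong class. If the placed class is then used as the outcome of a multinomial logit as though it had been observed, the misplaced participants mix the classes. The coefficients are then biased, and the intervals are centred on the wrong value, so they can cover the truth less often than stated.

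The sentence offers two ways to form classes and one regression for both. Under hard clustering the output is a label and nothing else, so the regression has no means of carrying uncertainty. Under a latent class model the correction is available but not named.

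At stake is the reliability of the factors reported as linked to patterns of PrEP use: real predictors may be diluted, and in some configurations a factor with no effect on a contrast may appear to have one.

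**Working it through.** **The plan's own figure.** This point disputes no stated number, but the sample size sets the scale. The section on sample size specifies power of 80%, 10% attrition, and a test "using the chi-square test for independence with two degrees of freedom, with an alpha of 0.05"; it also says "we use a more conservative effect size of 0.15". Reading 0.15 as Cohen's w, the required noncentrality is λ = 9.635. So N = λ / w² = 9.635 / 0.0225 = 428.2, rounded up to 429. Allowing for attrition, 429 / 0.90 = 476.7, rounded up to 477, or 159 per arm. The stated 160 per arm (480 in total) is reproduced to rounding. After attrition, 480 × 0.90 = 432, the n used in the main simulations.

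**Assumed inputs, not given in the documents.** Two or three classes; five binary indicators, one for each drug-level visit; one binary factor; the class profiles below.

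**Hand calculation, two classes.** Let each indicator be positive with probability h in the high class and 1 − h in the low class, and place a participant in the high class if at least three of five are positive. The misclassification probability is m = P(Bin(5, h) ≤ 2). Take true P(high) as 1/2 without the factor and 2/3 with it, so the true odds ratio is 2.0. The observed probability is p* = m + (1 − 2m)p, which stays at 1/2 without the factor.

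- h = 0.9: m = 0.0086; with the factor p* = 0.664; observed OR = 0.664 / 0.336 ≈ 1.97.
- h = 0.8: m = 0.058; p* = 0.647; observed OR = 0.647 / 0.353 ≈ 1.84.
- h = 0.7: m = 0.163; p* = 0.612; observed OR = 0.612 / 0.388 ≈ 1.58.

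**Simulation, n = 432.** Modal assignment followed by a logit on the assigned class was compared with a joint (one-step) likelihood. The measurement model was taken as known, a best case for both. There were 800 runs per two-class setting and 500 per three-class setting.

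| Setting | Entropy | Misplaced | True OR | Assigned class: OR (coverage) | Joint: OR (coverage) |
|---|---|---|---|---|---|
| 2 classes, h = 0.9 | 0.96 | 1% | 2.0 | 1.98 (0.95) | 2.00 (0.95) |
| 2 classes, h = 0.8 | 0.77 | 6% | 2.0 | 1.83 (0.93) | 2.00 (0.94) |
| 2 classes, h = 0.7 | 0.46 | 16% | 2.0 | 1.59 (0.79) | 2.01 (0.94) |
| 3 classes (never, early then stop, sustained), h = 0.9 | 0.82 | 8% | 2.0; 2.0 | 1.82 (0.94); 1.97 (0.94) | 2.00 (0.95); 2.00 (0.95) |
| Same, h = 0.8 | 0.56 | 20% | 2.0; 2.0 | 1.60 (0.85); 1.82 (0.91) | 1.97 (0.95); 2.03 (0.93) |
| 3 classes, middle overlapping top (0.05, 0.60, 0.92), two sets of runs | 0.68 | 14% | 1.0; 3.0 | 1.16–1.18 (0.92–0.94); 2.46–2.53 (0.88) | 0.98–1.01 (0.96–0.97); 3.00–3.08 (0.96) |

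The two-class rows agree with the hand calculation. The last row shows that the bias is not always toward zero: a null contrast moved to about 1.17. The Monte Carlo standard error of a coverage of 0.79 from 800 runs is √(0.79 × 0.21 / 800) = 0.014. Standard errors for the joint model come from a numerically differentiated Hessian. The optimiser's own approximation gave coverage as low as 0.815 around well-centred estimates and was not used.

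**Second set, measurement model estimated.** With 480 women, three classes, five binary visits, 200 runs per scenario, with and without drop-out, the true log odds ratio was 0.80. At entropy 0.62 to 0.71 the two-step estimate averaged 0.67 to 0.68, with coverage 0.87 to 0.90. At entropy 0.49 to 0.58 it averaged 0.55 to 0.57, with coverage 0.79 to 0.80. Attenuation therefore runs from 1 − 0.68/0.80 = 15% to 1 − 0.55/0.80 = 31%. Regression on the true class recovered 0.80 to 0.82.

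**The case against.** The strongest reply is that the article never says class will be assigned and treated as known. A latent class model with covariates uses a multinomial logit for membership, so the quoted words also describe one of the remedies. This is a condensed article, and an assignment rule is normal content for a full protocol or analysis plan that is not shown. This stands as a limit: a reader might infer that the plan commits to ignoring classification error, and the documents do not support that. It does not remove the point, because the article itself names hard clustering as an admissible route in so far as it leaves the clustering technique open, and joint latent class regression cannot be what is meant there.

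Other parts of the reply also stand:

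- A general claim of shrinkage toward zero would be wrong, as the overlapping-class result shows.
- Not every clustering method lacks membership probabilities; model-based and fuzzy clustering provide them.
- Five binary indicators are an assumption. Drug level is a continuous concentration, and the study also records attendance and dispensing. Richer indicators could separate the classes better.
- A reader might link this analysis to tailoring of the intervention. The sentence on tailoring belongs to the qualitative analysis paragraph, so the article does not make that link.

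**Conclusion.** The point holds as a minor, conditional one. The wording permits a classify-then-regress analysis that ignores classification error; it does not prescribe one, and no error in a stated figure is shown.

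The size turns on class separation, which the documents do not give. In the scenarios tried, the consequences were small at entropy of about 0.8 or more: coverage was about 0.94 to 0.95, and the worst estimate of a true odds ratio of 2.0 was 1.82. They were material at about 0.7 or less. At entropy of about 0.5 that odds ratio came out near 1.6, with coverage of 0.79 (two classes) to 0.85 (three classes). The usual direction is toward zero, but this is not assured with three or more classes. All of this rests on assumed class numbers, class profiles and indicators.

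Only the Aim 2 secondary outcome on factors associated with patterns of use is affected. The randomised drug-level comparison and the sample size do not depend on it.

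**What to change.** In Data analysis, state that associations between factors and PrEP-use class will be estimated either by one-step latent class regression or by a bias-adjusted three-step method (BCH or maximum-likelihood correction). Add that entropy and mean posterior probability by class will be reported, so that readers can judge how well the classes separate. Limit hard clustering to describing patterns, without regression on its labels.

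The cost is a sentence or two of wording and slightly more analysis work, with no new data. Intervals will be somewhat wider than those from the uncorrected regression.

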### Ethical considerations and trial registration

PrEP has been approved for use by international and domestic governing bodies in South Africa. Written informed consent will be obtained from participants at multiple time points, including prior to baseline questionnaire, PrEP initiation, and any qualitative interviews. The study protocol has received full ethical approval from the University of Cape Town Human Research Ethics Committee (Ref: 289/2018) and has been registered with ClinicalTrials.gov (NCT03977181). Any and all protocol modifications and annual ethics renewal will be submitted to the University of Cape Town Human Research Ethics Committee for approval.

There are no anticipated problems that are detrimental to the participants; however, expected clinical side effects of DIDIVIR include nausea, dizziness, and diarrhoea; study nurses will be trained on the Southern African HIV Clinicians Guidelines for PrEP used to identify and manage side effects [62]. All research staff will be trained to identify, probe for, and report AEs and social harms (SHs). Occurrence of AEs and SHs will be collected at every visit and recorded in REDCap. All AEs and SHs, with detailed study notes, will be internally reviewed by the study team. An AE list will be compiled and reviewed by the study DSMB and reported to University of Cape Town IRB. A study clinician will review all abnormal test results, liaise with local clinic doctors, and has the authority to terminate participants based on clinical opinion. Upon completion of their 2-year follow-up, all participants will be provided a referral to their local clinics for continuation of PrEP services.

### Dissemination plans

As results are available and finalized, they will be analysed for publication in peer-reviewed scientific journals and presentation at relevant scientific conferences; standard authorship guidelines will be followed, and no professional writers will be used. Results will also be presented, orally and in writing, to local (i.e. Buffalo City Metro District Department of Health), provincial (i.e. Eastern Cape Provincial Department of Health, Eastern Cape Provincial AIDS Council), and key national (i.e. South African National Department of Health, South African National HIV Think Tank) stakeholders. Results will be reported back to study CABs, communities and participants, via town hall style meetings and as 1-pager flyers using infographics. Key interim results (i.e. # HIV seroconversions, STI incidence, and pregnancies), implementation experiences, and lessons learned will be shared with district and provincial stakeholders on a bi-annual basis.

## Discussion

The Community PrEP Study is an innovative, mixed-methods study that aims to provide robust insights into (1) the acceptability, feasibility, and uptake of PrEP as a methods for HIV prevention by AGYW when delivered through CBCT platforms, (2) community-based prevention-effective adherence support for AGYW, and (3) the cost-effectiveness of such community-based approaches to delivering PrEP services. Numerous barriers have been described that delay or block AGYW from accessing clinic-based health services, especially reproductive health and HIV testing and prevention services. Consequently, reaching AGYW at scale with HIV prevention services requires delivery platforms outside of clinic-based facilities. Our use of community-based platforms to increase AGYW’s access to PrEP and provide same-day initiation is novel. If found to be acceptable and feasible, CBCT platforms can be used to target PrEP services to other at-risk and key populations.

Recent work has highlighted that positive peer support [63–65] and cognitive-behavioural problem-solving [46, 66] consistently improve medication adherence among adults and adolescents. Peer norms play an important role in shaping behaviours, especially for adolescents and young people [67, 68], and community-based approaches that build on peer support may have a strong influence on young women. Our group-based health clubs are highly innovative because they will (1) draw on peer support and cohesion to promote prevention-effective adherence to PrEP to prevent HIV infection, (2) provide a forum for adherence support outside the formal clinic environment, (3) create a positive group norm around the use of PrEP, and (4) provide a space to build social relationships and bonds with other AGYW who are using PrEP. If found to be effective, our prevention-effective adherence support interventions may be tailor for other at-risk groups and communities. Finally, given South Africa’s embrace of group-based ART adherence programmes [69, 70], our adherence support intervention will be well positioned to be integrated into South Africa’s current adherence support strategies.

Our study has both benefits and limitations of note. Many PrEP studies involving AGYW have required participants to be sexually active and/or “at-risk” [18–20, 71, 72]. By eliminating these inclusion criteria, we may be able to extend PrEP services and study involvement to AGYW that provide socially desirable answers to sexual activity and risk behaviour questions. Another benefit will be the provision of regular HIV and STI testing, and hepatitis B vaccination services. Though similar services are provided by local health clinics, participants may perceive or truly experience diminished barriers due to the nature and positioning of our community-based services. Of concern, by randomizing participants to a specific support modality, we may be overlooking the specific and/or unique needs and life-styles of individuals. As such, poor efficacy of an intervention arm may not be the true result of the modality itself, but due to the poor matching of a behavioural intervention to individuals. By conducting in-depth interviews with participants, we expect to assess this potential limitation. Finally, the ability to quickly form health club groups with a critical mass of participants will be impacted by the pace of recruitment. To minimize this potential challenge, study staff will closely monitor recruitment rates and initially create smaller groups that can be merged over time to ensure group critical mass. Moreover, given school, work, and familial responsibilities, scheduling of health clubs to ensure consistent attendance by a critical mass of participants may be logistically challenging. To address this, health clubs will be flexibly scheduled to maximize participant attendance.

Findings from our study will provide insight into uptake and prevention-effective use of PrEP to prevent HIV infection by AGYW in both urban and rural contexts. Identifying a prevention-effective adherence intervention suitable for this key population will provide researchers and clinicians with an additional tool integral for the rollout of PrEP. The cost-effectiveness analysis will provide policy makers with the information they need to make evidence-based decisions on the structure and components for a PrEP programme. Finally, the results of our study aim to inform approaches and guidelines related to PrEP programme implementation, rollout, and scale-up in South Africa and other sub-Saharan countries.

### Trial status

This trial was retrospectively registered with ClinicalTrials.gov (NCT03977181) on June 6, 2019. Participant recruitment was initiated on October 22, 2018, with enrolment completion on November 15, 2019. Participant follow-up will continue through November 2022. Protocol version 1.5, 22 May 2019.

## Data Availability

Study investigators ([name] and [name]) will provide the full study protocol, study data, and statistical code and adherence support materials upon reasonable request and approval of an appropriate data sharing agreement.

## Abbreviations

HIV: Human immunodeficiency virus
AGYW: Adolescent girls and young women
PrEP: Pre-exposure prophylaxis
FTC: Emtricitabine
TDF: Tenofovir
STI: Sexually transmitted infections
CBCT: Community-based HIV counselling and testing
CAB: Community advisory boards
BCM: Buffalo City Metro
IMB: Information-Motivation-Behavioural Skills Model of Behaviour Change
REDCap: Research Electronic Data Capture
ACASI: Audio computer-assisted self-interviewing
PEP: Post-exposure prophylaxis
IDI: In-depth interviews
CME: Community mapping exercises
FGD: Focus group discussion
SEP: Staff exchange programmes
HBsAg: Hepatitis B antigen
eGRF: Estimated glomerular filtration
DBS: Dried blood spot
DALY: Disability-adjusted life years
AE: Adverse events
SH: Social harms
CT: *Chlamydia trachomatis*
NG: *Neisseria gonorrhoeae*
TV: *Trichomonas vaginalis*
